### Economic evaluation

The economic evaluation aims to compare the costs generated by pregnant women receiving routine third trimester ultrasound screening versus those receiving CAU. Both a cost-effectiveness and cost-utility analysis will be conducted using different perspectives and time horizons.

#### Cost‐effectiveness and cost‐utility analyses

First, we will perform a cost‐effectiveness analysis from a healthcare perspective. The time horizon of this analysis ranges from 22 weeks of gestation to one week after the date of birth of the child. In this analysis, pregnancy related data derived from the Perined database of all 15,000 participating women will be used. Detailed cost data collected by research assistants/nurses from medical records of women participating in the random (*n* = 900) and non-random sample (*n* = 600) will be used to estimate the healthcare costs for the whole study population (*n* = 15,000) using Bayesian techniques in combination with Monte Carlo simulation. Incremental Cost‐Effectiveness Ratios (ICER) will be calculated by dividing the difference in healthcare costs by the difference in effects.

Second, we will perform a cost‐effectiveness analysis from a societal perspective. The time horizon of this analysis ranges from 22 weeks of gestation until 6 months after the estimated date of delivery. Again, pregnancy related data derived from the Perined database of all 15,000 participating women will be used in this analysis. Detailed cost data collected by research assistants/nurses from medical records, and self-report utilization and lost productivity data of women participating in the random (*n* = 900) and non-random (*n* = 600) sample will be used to estimate societal costs for the whole study population (*n* = 15,000) by applying Bayesian techniques in combination with Monte Carlo simulation. Furthermore, the combination of direct costs and indirect costs (based on maternal reports of absenteeism and presenteeism at (unpaid) work measured with the iPCQ [29]) will be related to the composite of severe adverse perinatal outcome to estimate the ICER.

Finally, a cost‐utility analysis from a societal perspective will be performed. The time horizon of this analysis ranges from 22 weeks of gestation until 6 months after the expected date of delivery. For this analysis, data of the 900 women in the random sample will be used. Quality‐Adjusted Life‐Years (QALYs) will be calculated based on the EQ‐5D‐5 L using the Dutch tariff) [48]. Incremental Cost‐Utility Ratios (ICURs) will be calculated by relating the difference in costs between the conditions to the difference in QALYs. In this analysis, missing cost and effect data will be imputed using multiple imputation based on the MICE algorithm developed by Van Buuren et al. (1999) [49]. Bias‐corrected and accelerated bootstrapping with 5000 replications will be used to estimate 95 % confidence intervals around cost differences and the uncertainty surrounding the ICERs and ICUR.

Both the cost‐effectiveness and cost‐utility analyses will be conducted using an intention‐to‐treat approach. For all analyses uncertainty surrounding the ICERs and ICUR will be graphically presented on cost‐effectiveness planes. Cost‐effectiveness acceptability curves will also be estimated using the net benefit framework [50]. Cost‐effectiveness acceptability curves will illustrate the probability that routine third trimester ultrasound screening for IUGR is cost‐effective (or not) as compared to CAU for a range of various ceiling ratios thereby demonstrating decision uncertainty.

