#### Primary outcome – severe adverse perinatal outcome

The primary dichotomous clinical outcome of the main study will be a composite measure of severe adverse perinatal outcomes up to 7 days after birth defined as one or more of the following:Antepartum, intrapartum or perinatal death occurring from 28 weeks of gestation onwardApgar score <4 at 5 min after birth;Coma, stupor or decreased response to pain up to 7 days after birth;Asphyxia, defined as cord blood arterial base excess of less than minus 12;Neonatal seizures defined as clonic movements which cannot be stopped by holding the limb, occurring on two or more occasions before 72 h of age;Assisted ventilation for more than 24 h via endotracheal tube initiated within 72 h after birth;Septicemia, ascertained by a positive blood culture;Meningitis, ascertained by positive cerebrospinal fluid culture;Bronchopulmonary dysplasia (BPD), defined as need for oxygen at a postnatal gestational age from 36 completed weeks as well as an X‐ray compatible with BPD;Intraventricular hemorrhage, defined as grade 3 or 4 and diagnosed by cranial ultrasound or at autopsyCystic periventricular leukomalacia (PVL), diagnosed by cranial ultrasound or at autopsy showing periventricular cystic changes in the white matter excluding subependymal and choroid plexus cysts;Necrotizing enterocolitis, defined as either perforation of intestine, pneumatosis intestinalis or air in the portal vein, diagnosed by X‐ray or surgery, or at autopsy.

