#### Primary outcome - costs

Healthcare costs will include costs related to pregnancy-related healthcare use, including community midwife consultations, referrals to specialist care, ultrasound examinations, laboratory tests, CTG monitoring, hospital admission, interventions during labor, and admission to neonatal unit. Healthcare costs will be calculated using standard costs published in the Dutch costing guidelines [28]. Medication use will be calculated using prices of the Royal Dutch Society for Pharmacy.

Absenteeism and presenteeism at work (indirect costs) as reported by (pregnant) women will be assessed by the iMTA Productivity Cost Questionnaire (iPCQ) [29].

The friction cost approach will be used to estimate indirect costs using Dutch age and sex specific lost productivity costs [30, 31].

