#### Secondary outcomes – single outcomes

Single outcomes include the different elements of the composite primary outcome and the secondary composite outcome. Other secondary single outcomes will be neonatal mortality and severe morbidity between the 7th and 28th day after birth, congenital abnormalities, life threatening congenital conditions among neonates, non‐cephalic presentations (when labor started) in primary care, and place of birth. Mean birth weight, low birth weight, macrosomia, mean gestational age, and prematurity will also be single secondary outcomes.

Other secondary single outcomes, that will be reported by women participating in the survey (*n* = 1500), will include 1) maternal prenatal and postnatal quality of life (EQ‐5D‐5 L and one item of the short form health survey (SF-36) [32–34]); 2) maternal experience of continuity of healthcare and satisfaction with healthcare during pregnancy and delivery (Nijmegen Continuity Questionnaire (NCQ) and Pregnancy and Childbirth Questionnaire (PCQ)) [35, 36]; 3) maternal pre- and postnatal anxiety and pregnancy-specific anxiety (State and Trait Anxiety Inventory (STAI) [37], and the Pregnancy Anxiety Questionnaire-Revised (PRAQ-R)) [38]; 4) and pre- and postnatal depressive symptoms (Edinburgh (Postpartum) Depression Scale) [39, 40]; and 5) prenatal and postnatal maternal bonding, i.e., the emotional tie between the mother and the (unborn) child (Maternal Antenatal Attachment Scale (MAAS) and Maternal Postnatal Attachment Scale (MPAS)) [41, 42]. Moreover, other secondary single outcomes will be infant developmental milestones at age 6 months assessed with the Ages and Stages Questionnaire (ASQ) and toddlers’ behavioral problems and developmental milestones at 24 months measured via the Child Behavior Checklist (CBCL) and ASQ, respectively [43–45].

In a purposively selected subsample of pregnant women (n ~ 15) participating in the intervention group, semi-structured interviews will be conducted during late pregnancy to explore and better understand the role of third trimester ultrasound screening in the experience of maternal pregnancy-specific anxiety and maternal bonding.

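### The healthcare-perspective cost-effectiveness analysis stops one week after birth, so it omits all neonatal care cost after day 7 and its ICER is incomplete, by an unknown amount and in an unknown direction

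*Protocol article*

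**What the plan says.** The section *Cost-effectiveness and cost-utility analyses* sets the horizon of the healthcare-perspective analysis: "The time horizon of this analysis ranges from 22 weeks of gestation to one week after the date of birth of the child". Its ICER is the difference in healthcare costs divided by the difference in effects.

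The section *Primary outcome - costs* lists the healthcare items to be costed, among them "hospital admission, interventions during labor, and admission to neonatal unit".

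The clinical primary outcome is a "composite measure of severe adverse perinatal outcomes up to 7 days after birth". One of its components is "Bronchopulmonary dysplasia (BPD), defined as need for oxygen at a postnatal gestational age from 36 completed weeks". A separate secondary outcome is "neonatal mortality and severe morbidity between the 7th and 28th day after birth".

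A second cost-effectiveness analysis takes the societal perspective and has a longer window: "The time horizon of this analysis ranges from 22 weeks of gestation until 6 months after the estimated date of delivery". It relates "the combination of direct costs and indirect costs" to the same composite.

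The article gives no reason for the one-week limit.

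**The concern.** The seven-day limit does different things to the two parts of the ratio. For the composite, it limits when an event may occur. For costs, it cuts off the bill for an event that has already been counted. A severe outcome averted counts in full in the denominator, while any treatment it would have needed after day 7 is missing from the numerator. Routine scans, referral, extra monitoring and induction all come before the cut-off, so their costs are complete.

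Costs are listed as a primary outcome, and the *Discussion* says the results are meant to help healthcare providers and policymakers decide whether to introduce routine scanning. The healthcare perspective speaks most directly to a payer, and it is the one with the truncated costs.

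**Working it through.** **Inputs from the protocol article**
- Cost window of the healthcare analysis: 22 weeks of gestation to day 7 (*Cost-effectiveness and cost-utility analyses*).
- Target event rates: 1.54% and 1.0% (*Sample size of the trial*).
- Group size: 7,500 per condition (*Abstract*, Methods).
- Length of stay, cost per day and component frequencies: not given. The plan therefore has no figure of its own on this point to reproduce.

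**Effect unit.** The healthcare paragraph speaks only of effects. Using the composite is an inference, but a reasonable one: *Research aims* frames cost-effectiveness in terms of reducing that outcome, and the societal paragraph names it.

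**Step 1: can a counted event cost money after day 7?** Yes, on the article's own definitions. BPD requires oxygen need from 36 completed weeks. A baby born at 30 weeks reaches that point on day 6 × 7 = 42, which is 42 − 7 = 35 days after the cost window closes. For any birth before 35 weeks, day 7 comes before the point at which BPD is defined.

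**Step 2: what the cut does to the ICER.** Let E be the events averted, D the admission days after day 7 per averted event, c the daily cost, and H the cost after day 7 of any admissions that screening adds.
- Reported ICER = (cost difference to day 7) / E.
- Complete ICER = (cost difference to day 7 − E·D·c + H) / E.
- Reported − complete = D·c − H/E.

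The difference is positive (against screening) if the averted care dominates, negative (in favour of screening) if the added care dominates, and zero if they cancel. The article supplies none of D, c or H.

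**Step 3: share of a single stay omitted.** With a stay of L days from birth and a flat daily cost (both assumptions), the share is max(0, 1 − 7/L).

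| L (days) | Share after day 7 |
|---|---|
| 7 or less | 0% |
| 10 | 30% |
| 14 | 50% |
| 21 | 67% |
| 42 | 83% |

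**Step 4: mixed stays.** Suppose a fraction f of events stay L days and the rest stay 5 days (assumed). The omitted share is f(L − 7) / [fL + 5(1 − f)]. It reaches one half at f ≈ 42% for L = 21 and at f ≈ 15% for L = 42. At f = 10% and L = 42 it is 3.5/8.7 = 40%.

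**Step 5: scale at the planned effect.** E = 7,500 × (0.0154 − 0.0100) = 40.5. If every averted event had D = 7, 14 or 35 days after day 7 (L = 14, 21 or 42), the days left out would be 40.5 × D ≈ 284, 567 or 1,418. At D = 0 nothing is left out. These figures show the scale only; they are not estimates, because the events in the composite differ widely in the stay they cause.

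**The case against.** **The 6-month analysis already covers later costs.** This is the strongest point, and much of it stands. The societal analysis carries direct costs past day 7 against the same composite, so a reader who inferred that the economic evaluation as a whole ignores care after the first week would be mistaken. Productivity losses are measured with their own questionnaire and valued separately, so the direct part can be extracted. What remains is that the article announces no healthcare-only ICER beyond week 1. The two planned analyses also differ in perspective and horizon at once, so a difference between their ICERs could not be attributed to either.

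**Cost and effect windows are both seven days and apply equally to both arms.** This is true in form. But the composite's window limits the occurrence of an event, not its cost, and for BPD after a birth before 35 weeks the defining point lies outside the cost window. The day 7 to 28 morbidity outcome is separate from the composite, so it shows only that the trial looks beyond week 1.

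**Not every event causes a long stay.** This stands. The composite includes death, a 5-minute Apgar score below 4, and asphyxia defined by cord blood alone. None of these requires a long admission, and a stillbirth has no neonatal stay at all. A reader might infer that most of the neonatal admission cost is dropped. At a flat daily cost that needs a cost-weighted stay above 14 days, and the documents give no stay to support it.

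**Conclusion.** The point holds in a limited form. One of the two planned cost-effectiveness analyses leaves out all neonatal cost after day 7 while counting screening and antenatal costs in full, and no reason is given. Its ICER is incomplete.

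Two stronger conclusions are not supported. One is that the healthcare result must be wrong, or must be biased against screening: averted outcomes push one way, added early deliveries and admissions push the other, and the net sign is unknown. The other is any specific size for the omission: the shares in the table rest on assumed stays and a flat daily cost, and range from nothing upward.

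The conclusion also rests on reading the composite as the effect in the healthcare analysis, which the article implies but does not state in that paragraph. The change is worth making because it is cheap and removes a truncation that a payer would otherwise have to guess at.

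**What to change.** Report a healthcare-perspective ICER that uses the direct-cost part of the already planned 6-month analysis, with productivity losses left out. Alternatively, carry healthcare costs to the child's first discharge. Name the severe-outcome composite as the effect in that paragraph. Keep the one-week result as a secondary view, and state that it excludes neonatal costs after day 7.

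A day-28 cut-off would be a weaker remedy: a 40-day stay, for example, would still lose 12 of 40 days (30%).

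The cost is small. Direct costs to 6 months are already planned, and *Hospital medical records* already provides for abstracting healthcare use for neonates referred for admission, with no day-7 limit stated. The downsides are a wider cost variance, because a few long stays will carry weight, and slightly more abstraction for those stays.

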#### Survey

Two subsamples will be derived from the complete study population (see Fig. 1) for a detailed assessment of societal costs, maternal quality of life, maternal experience of healthcare during the perinatal period, maternal psychological functioning (maternal depressive symptoms, anxiety, and bonding), and infant neurodevelopment. These two subsamples comprise the following: (a) a random sample of 900 women (450 intervention and 450 CAU) who will be asked to complete online questionnaires around 22 weeks of gestation, at 32 weeks of gestation, and at 6 weeks, 6 months, and 24 months after estimated date of delivery (*n* = 15 per midwifery practice); and (b) a non-random sample comprising 600 women in whom IUGR is suspected by fetal ultrasonography (300 intervention and 300 CAU) and who will be asked to complete online questionnaires (*n* = 10 per midwifery practice) after the suspicion of IUGR during late pregnancy, at 6 weeks and 6 and 24 months postpartum. At the age of 24 months, we will ask mothers participating in the survey and mothers of toddlers having (a) severe adverse perinatal outcome(s) (see above for the definition of our primary clinical outcome) to report toddlers’ developmental milestones and behavioral problems.

For the survey, we will recruit 1500 women prenatally. Based on an expected non-response and drop-out rate of 33 %, we expect to collect complete follow-up data in 1000 women in the random (*n* = 600) and non-random sample (*n* = 400).

Women who will participate in the survey will give additional consent to participate in the survey and will receive an e-mail with a link to an online questionnaire at each measurement time point. Non-responding pregnant women will receive reminders via e-mail. To enhance participation of non-Dutch speaking women, the questionnaires will be translated into English. These questionnaire data will be collected through telephone interviews conducted by a researcher.

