#### Effectiveness analyses

First, we will compare baseline characteristics of women participating in the intervention and control group using independent t-tests and chi-square tests. Second, we will compare baseline characteristics of drop-outs and completers by using independent t-tests and chi-square tests. Third, we will perform multiple logistic multilevel regression analysis to test the possible effect of routine third trimester ultrasound screening on severe adverse perinatal outcome. This analysis will be adjusted for possible clustering of observations at the level of midwifery practices and medical/biological, demographic and life-style related confounders. In all analyses, we will use an intention-to-treat approach and set the level of significance at *p* < 0.05.

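### The cost-utility analysis states no adjustment of the QALY difference for 22-week EQ-5D-5L utility, a covariate that should already be in hand and would make the estimate more precise

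*Protocol article*

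**What the plan says.** Under Cost-effectiveness and cost-utility analyses, the protocol article states that ICURs "will be calculated by relating the difference in costs between the conditions to the difference in QALYs". On the horizon it says: "The time horizon of this analysis ranges from 22 weeks of gestation until 6 months after the expected date of delivery". On the sample it says: "For this analysis, data of the 900 women in the random sample will be used". The same section specifies the Dutch EQ-5D-5L tariff, multiple imputation by MICE, bias-corrected and accelerated bootstrapping with 5000 replications, cost-effectiveness planes, and acceptability curves in the net benefit framework. It names no covariate and no regression model for the QALY difference.

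The Survey section describes those women as "a random sample of 900 women (450 intervention and 450 CAU) who will be asked to complete online questionnaires around 22 weeks of gestation", with later questionnaires "at 32 weeks of gestation, and at 6 weeks, 6 months, and 24 months after estimated date of delivery". The outcome list places the EQ-5D-5L under "maternal prenatal and postnatal quality of life" without assigning it to particular visits. The Intervention section puts the first routine scan at 28–30 weeks.

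Covariate adjustment is stated once, under Effectiveness analyses, and there it belongs to the primary clinical model: "This analysis will be adjusted for possible clustering of observations at the level of midwifery practices and medical/biological, demographic and life-style related confounders".

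**The concern.** A QALY total that runs from 22 weeks needs a utility value at 22 weeks, and that value is the first point of each woman's curve. It precedes the first routine scan, so a difference between conditions at that point cannot be an effect of the scans. It still reaches an unadjusted QALY difference in two ways: directly, as part of the area under the curve, and indirectly, through its correlation with later utility.

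Imputation and bootstrapping do not take it out. The bootstrap describes the resulting uncertainty but does not reduce it.

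At stake is the precision of the incremental QALY, and therefore of the ICUR, the plane and the acceptability curve. There is also a choice between an adjusted and an unadjusted estimate, which is better fixed before results are seen.

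**Working it through.** **The plan's own figures.** The article gives no power, SD or standard error for the cost-utility analysis, so there is no such figure to reproduce. The one figure tied to this sample is the expected number of completers: 900 × (1 − 0.33) = 603, stated as 600.

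**Inputs from the article.** 450 women per condition. Questionnaires at 22 and 32 weeks of gestation and at 6 weeks and 6 months after the due date. The 24-month questionnaire falls outside the horizon.

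**Assumptions (not in the article).**
- EQ-5D-5L is measured at each of the four visits.
- Term is 40 weeks and 6 months is 26 weeks, so the visits fall at weeks 22, 32, 46 and 66.
- Utility SD is 0.15 at every visit.
- Between-visit correlation ρ is 0.3, 0.5 or 0.7. It is either equal for all pairs of visits, or decays as ρ, ρ², ρ³ with one, two or three visits between measurements.
- Clustering and period effects are ignored.

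**Step 1: weights.** The intervals are 10, 14 and 20 weeks. The trapezoid weights w are 5, (10+14)/2 = 12, (14+20)/2 = 17 and 10. They sum to 44 weeks, or 44/52 = 0.846 years.

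**Step 2: formulas.** Let C be the weighted sum of each visit's correlation with the 22-week value. Let V be the weighted quadratic form w′Rw, where R is the correlation matrix.
- Share of QALY variance explained by baseline utility, and so removed by adjustment: C²/V.
- QALY shift per unit of baseline utility: C/52.
- Unadjusted SE: 0.15 × √V/52 × √(2/n), with n women per condition.
- Adjusted SE: the unadjusted SE × √(1 − C²/V).

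The sum of squared weights is 25 + 144 + 289 + 100 = 558. The products of weights are:
- adjacent visits: 60 + 204 + 170 = 434
- two apart: 85 + 120 = 205
- three apart: 50

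**Step 3: worked case, ρ = 0.5.**
- Equal correlation: C = 5 + 0.5 × 39 = 24.5. V = 558 + 2 × 0.5 × 689 = 1247. C²/V = 600.25/1247 = 0.481.
- Decaying correlation: C = 5 + 6 + 4.25 + 1.25 = 16.5. V = 558 + 2 × (217 + 51.25 + 6.25) = 1107. C²/V = 272.25/1107 = 0.246.

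**Step 4: all cases, 450 per condition.**

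| Correlation | ρ | C | V | Variance cut | QALY shift per 0.01 | SE unadjusted | SE adjusted |
|---|---|---|---|---|---|---|---|
| Equal | 0.3 | 16.7 | 971.4 | 29% | 0.0032 | 0.0060 | 0.0051 |
| Equal | 0.5 | 24.5 | 1247 | 48% | 0.0047 | 0.0068 | 0.0049 |
| Equal | 0.7 | 32.3 | 1522.6 | 69% | 0.0062 | 0.0075 | 0.0042 |
| Decaying | 0.3 | 10.4 | 858 | 13% | 0.0020 | 0.0056 | 0.0053 |
| Decaying | 0.5 | 16.5 | 1107 | 25% | 0.0032 | 0.0064 | 0.0056 |
| Decaying | 0.7 | 25.16 | 1400.8 | 45% | 0.0048 | 0.0072 | 0.0053 |

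With 300 completers per condition and equal ρ = 0.5, the SE falls from 0.0083 to 0.0060.

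The variance cut and the shift do not depend on the assumed SD; the standard errors do. The chance SE of the baseline difference is 0.15 × √(2/450) = 0.010, so a 0.01 imbalance is an ordinary one under the assumed SD.

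**The case against.** The strongest objection is that the article is silent and that silence is not a decision. The sentence on the ICUR is the ordinary definition of that ratio and fits an adjusted difference equally well. The ICER is defined in the same generic way, and its effect measure is an outcome that is analysed elsewhere in an adjusted model. Estimator details of this kind are often left to an analysis plan, and one may exist. This stands in part: a reader might infer that the plan has chosen an unadjusted comparison, and the text does not say so. What remains is that the section goes into detail on tariff, imputation, bootstrap and net benefit, gives no covariate, and sits beside a clinical analysis whose adjustment is stated for that analysis alone. Followed as written, it yields an unadjusted difference.

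A reader might also infer that chance imbalance biases the ICUR. It does not. Under randomisation it is sampling noise and already lies inside the bootstrap interval. Systematic imbalance is conceivable here, because condition is tied to calendar time and women enrol after their practice's condition is set. The article gives no evidence of its size, and adjusting for 22-week utility would not by itself remove period effects.

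Two further inferences fail. That imbalance would decide the sign of the ICUR is not shown, since nothing in the article gives the expected QALY difference or the cost variance. A gain in power has no target, since the section plans estimation and decision uncertainty, not a powered QALY test.

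Finally, the 22-week EQ-5D-5L is an inference from the horizon and the questionnaire schedule. It is a reasonable one, because QALYs from 22 weeks cannot be built by the usual area method without it.

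**Conclusion.** The point holds as an available improvement that the article does not take up; it is not a demonstrated error. The cost-utility section states no adjustment for 22-week utility, and a QALY difference computed as written carries any imbalance at that visit and gives up precision. The variance saving is about 13% to 69% and the shift about 0.002 to 0.006 QALY per 0.01 of imbalance. The width of that range comes from the unknown correlation structure. The lower end, with correlation that fades from pregnancy to six months after birth, is as plausible as the upper. The figures concern the QALY difference only; the effect on the ICUR and the acceptability curve also depends on costs and was not calculated.

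**What to change.** In the cost-utility paragraph, state that the incremental QALY is estimated by regression of QALY on condition with 22-week EQ-5D-5L utility as a covariate. It should be fitted jointly with the cost equation (for example by seemingly unrelated regression) and run within the planned multiple imputation and bootstrap. Base the ICUR, the plane and the acceptability curve on the adjusted differences, and report the unadjusted difference as a sensitivity analysis. Confirm in the Survey section that the EQ-5D-5L is part of the 22-week questionnaire.

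The cost is a few sentences and a little programming. No new data are needed, since the 22-week value is required for the QALYs anyway and missing values are already to be imputed. If an analysis plan already specifies this adjustment, a one-sentence reference to it settles the point.
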